### Statistical analyses

Baseline differences in demographic and clinical characteristics between the intervention and control groups will be evaluated by chi-square and independent sample *t* tests. All data will be analysed using the intent-to-treat principle. For outcome measures that are not normally distributed (e.g. the HAM-D-17), log transformation will be applied to perform the analyses. Mixed-effects models will be fitted for each outcome measure using baseline, 6th, 12th and 24th week follow-up data. Possible confounding factors such as sex, age, and use of antidepressant medication will be treated as time-dependent covariate in the mixed-effects models. If applicable, subgroup analysis will be carried out to estimate whether there is any gender difference (female versus male caregivers) regarding the effect of the intervention in alleviating depressive symptoms. Fixed effects for time, intervention group, and their interactions will be examined and unstructured covariance structure will be employed to account for the within-subject correlation over time. Levels of significance will be set at *p* < 0.05. All analyses will be performed using SPSS version 20.0 (SPSS Inc., Chicago, IL, USA).

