### Primary outcome

Participants will be assessed at baseline, 6th week, 12th week and 24th week for their responses to intervention. The assessment schedules for caregivers and care recipients are described in Table 1. The primary outcome of the study is the proportion of participants who are classified as responders by the Hamilton Rating Scale for Depression (HAM-D-17) [35]. HAM-D-17 is a widely used and reliable measure of depressive symptoms. The scores range from 0 to 52, with higher scores indicating greater depression severity. Response to the intervention is defined as a reduction of the HAM-D-17 total score by ≥50 % from baseline to endpoint. Assessors will follow the structured interview guide for the Hamilton Depression Rating Scale (SIGH-D) when administering the HAM-D-17 [36].

**Table 1 Tab1:** Assessment schedule for caregivers and care recipients

	Baseline assessment	Week 6	Week 12	Week 24
Caregiver only				
GDS (screening only)	√			
HAM-D-17	√	√	√	√
ZBI	√	√	√	√
SF-12	√		√	√
EXIT25	√		√	√
IPIP	√			
Care recipients only				
CSDD	√	√	√	√
NPI	√		√	√
DAD	√		√	√
MBI	√		√	√
Caregivers and care recipients				
MMSE	√		√	√
Digit span	√		√	√
Delayed recall	√		√	√
CVFT	√		√	√
BBS	√		√	√
FR	√		√	√
TUG	√		√	√
Logbook	√	√	√	√
Pedometer	√	√	√	√
*BDNF* genotype	√			
Body weight and height	√		√	√
Blood pressure and pulse	√		√	√

*BBS* Berg Balance Scale, *BDNF* brain-derived neurotrophic factor, *CSDD* Cornell Scale for Depression in Dementia, *CVFT* Category Verbal Fluency Test, *DAD* Disability Assessment for Dementia, *EXIT25* Executive Interview, *FR* Functional Reach, *GDS* Geriatric Depression Scale, *HAM-D-17* Hamilton Rating Scale for Depression, *IPIP* International Personality Item Pool, *MBI* Modified Barthel Index, *MMSE* Mini Mental State Examination, *NPI* Neuropsychiatric Inventory, *TUG* Timed Up and Go, *ZBI* Zarit Burden Interview

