Assessment for both caregivers and care recipients:Sociodemographic information includes age, gender, education level and marital statusLifestyle factors such as smoking, drinking, and sleeping habits. Health-related information like chronic health problems and medications will also be recorded. Resting blood pressure and heart rate will be taken. Body height and weight will also be measured to calculate Body Mass IndexGlobal cognitive function will be measured by the MMSE [29], digit span, delayed recall, and the Category Verbal Fluency Test (CVFT) [45]Balance ability and functional mobility will be measured by the Berg Balance Scale (BBS) [46], the Functional Reach (FR) test [47], and the Timed Up and Go (TUG) test [48]Physical activity and programme adherence will be assessed using logbook recordings. Before each assessment, participants will be asked to wear a pedometer for 1 week. Number of walking steps, history of falls, frequency, duration, and type of exercises during the week will be recorded in the logbookPhysiological markers – to examine the role of the *BDNF* Val66Met polymorphism in the antidepressant effect of exercise, buccal swabs will be collected at the baseline assessment

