## Discussion

Since the prevalence of dementia doubles every 5 years after the age of 60, population ageing inevitably increases the number of persons with dementia. Hong Kong is no exception to this trend. It is estimated that around one in 10 local older persons are now suffering from dementia [50].

Caregiving for persons with dementia is demanding and challenging. Evidence shows that it adversely affects caregivers’ physical [51] as well as mental wellbeing [3–5], including a vulnerability to developing depression. In a review of 10 studies involving 790 caregivers of persons with dementia, more than one fifth of them suffered from a depressive disorder [3]. The prevalence of depressive symptoms among caregivers is even higher [14].

This study will investigate the efficacy of a structured exercise programme in alleviating depressive symptoms among caregivers of persons with dementia. We focus on caregivers with depressive symptoms instead of depressive disorders as the former constitute the largest group of depressed caregivers. Besides, because of ethical concerns, we will refer those who suffer from clinically significant depression to appropriate agencies for psychiatric assessment and treatment.

The intervention is tailor-made for family caregivers in three ways. First, the programme is delivered at participants’ homes to facilitate their participation. Second, both caregivers and care recipients will be involved in the study. Third, a moderate-intensity aerobic exercise that has been successfully implemented in the local older population (i.e. sitting Tai Chi) is chosen as the intervention.

Sitting Tai Chi is a safe, low-impact and low-cost exercise intervention. If it is shown to improve caregivers’ mood, it will offer a potentially effective treatment alternative for depression among caregivers of persons with dementia. In addition, we expect that home-based exercise will also benefit the care recipients.

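### Antidepressant use is adjusted for as a time-dependent covariate, so the model conditions on a post-randomisation variable and does not target the intention-to-treat effect; baseline use should be the covariate

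*Protocol article*

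**What the plan says.** The Statistical analyses section of the protocol article names possible confounders and sets the covariate rule: "sex, age, and use of antidepressant medication will be treated as time-dependent covariate in the mixed-effects models". It describes the data entering those models: "Mixed-effects models will be fitted for each outcome measure using baseline, 6th, 12th and 24th week follow-up data". It describes the treatment terms: "Fixed effects for time, intervention group, and their interactions will be examined". The same paragraph commits to a principle: "All data will be analysed using the intent-to-treat principle".

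Three other places bear on the point.

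- **Inclusion criteria.** Caregivers who take an antidepressant must have been on an unchanged dose for three months or more. The item is marked as applying only where relevant, so caregivers not on antidepressants are eligible. Nothing is said about use after entry.
- **Primary outcome (assessments for both members of the dyad).** "Health-related information like chronic health problems and medications will also be recorded". Table 1 has no medication row, so the visits at which this happens are not shown.
- **Discussion.** After explaining that the trial enrols caregivers with symptoms and not disorders, the authors write that "we will refer those who suffer from clinically significant depression to appropriate agencies for psychiatric assessment and treatment".

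**The concern.** Of the four values of a time-dependent antidepressant variable, three are measured after randomisation. A caregiver whose mood worsens may start a drug, and a caregiver whose mood improves may not need one. If the exercise programme changes mood, it can change drug use, and drug use can change the HAM-D-17 score. A variable on that path is not a confounder of a randomised comparison, since allocation already removes systematic confounding at baseline.

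Conditioning on it has two consequences. Current use acts partly as a marker of poor mood, so adjusting for it can absorb some of the treatment effect. If the drug works and controls start it more often, adjusting for it also removes help that the controls really received, which can inflate the effect. In both cases the group-by-time terms stop estimating the total effect of being allocated to exercise. Where such a shift exists, a larger sample does not remove it.

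The mixed model is the only treatment-effect analysis named, and it applies to every outcome.

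**Working it through.** **What the documents supply.** The covariate rule, the four visits, the group, time and interaction terms and the unstructured covariance come from Statistical analyses. The entry rule comes from Inclusion criteria. No section gives a rate of antidepressant starts, stops or changes, a drug effect or a HAM-D-17 standard deviation. There is therefore no figure of the plan's own to reproduce, and everything numerical below is an assumption used to show a range.

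**Sex and age.** Sex is constant. Age moves by at most 24/52 = 0.46 year over the study. The time-dependent form changes nothing of substance for these two, so its whole effect falls on antidepressant use.

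**Simulation.** There were 150,000 subjects per scenario, with visits at baseline and weeks 6, 12 and 24. The outcome is continuous with an SD of about 1. The assumed direct effect of exercise is 0, -0.25, -0.50 and -0.50 SD at the four visits (set to 0 throughout in the no-effect scenario). Baseline antidepressant use is 10%. Drug starts follow a logistic function of mood, either current mood or mood at the previous visit. The drug effect is 0, -0.5 or -0.8 SD. The model is generalised least squares with visit terms, group-by-visit terms and an unstructured covariance. It was fitted with baseline use or with time-dependent use to the same simulated data, so differences within a row are not sampling noise.

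Change = (time-dependent estimate - baseline-covariate estimate) / baseline-covariate estimate. Each cell gives week 12, then week 24. Starters are new users, control / Tai Chi.

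| Starts follow | Drug effect | Starters wk 12; wk 24 | Baseline use as covariate | Time-dependent use | Change |
|---|---|---|---|---|---|
| current mood | 0 | 2/1%; 4/2% | -0.495, -0.502 | -0.493, -0.499 | 0.4%, 0.6% smaller |
| current mood | 0 | 16/11%; 23/15% | -0.495, -0.502 | -0.468, -0.464 | 5%, 8% smaller |
| current mood | 0 | 26/19%; 35/24% | -0.495, -0.502 | -0.453, -0.445 | 8%, 11% smaller |
| current mood, steeper | 0 | 34/23%; 43/29% | -0.495, -0.502 | -0.415, -0.401 | 16%, 20% smaller |
| current mood, steeper | -0.8 | 34/23%; 43/29% | -0.407, -0.391 | -0.397, -0.378 | 2%, 3% smaller |
| current mood | -0.8 | 26/19%; 35/24% | -0.433, -0.416 | -0.440, -0.427 | 2%, 3% larger |
| previous mood | -0.8 | 22/20%; 30/26% | -0.494, -0.469 | -0.504, -0.495 | 2%, 6% larger |
| previous mood, steeper | -0.5 | 30/27%; 39/32% | -0.491, -0.467 | -0.503, -0.494 | 2%, 6% larger |
| unrelated to mood | -0.5 | 17/17%; 24/24% | -0.506, -0.501 | -0.506, -0.501 | none |
| current mood, no exercise effect | -0.5 | 26/26%; 35/35% | 0.006, -0.001 | 0.007, 0.000 | none visible |

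In the scenarios where an unadjusted model was also fitted (previous mood, and starts unrelated to mood), adjusting for baseline use gave the unadjusted total effect to three decimals. Baseline adjustment leaves the target intact.

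**Scale against random error.** With the 56 dyads per arm in Sample size calculation, a simple difference on an SD-1 scale has a standard error of sqrt(2/56) = 0.189. The largest attenuation is 0.502 - 0.401 = 0.101 SD, about half a standard error (0.101/0.189 = 0.53). The largest overstatement is 0.494 - 0.467 = 0.027 SD, about one seventh (0.027/0.189 = 0.14).

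**The case against.** Four arguments can be made for the plan.

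1. **Drug changes may be rare.** Enrolled caregivers score below the local cut-off for clinically significant depression, and those on antidepressants enter on an unchanged dose. With 2-4% new starters in the control arm the shift is at most 0.003 SD. This stands, and it limits what can be said about size.
2. **The referral sentence does not prove in-trial starts.** A reader might infer from the Discussion that depressed participants will be sent for treatment during follow-up, so that drug starts driven by the outcome are built into the trial. The documents do not support that. The sentence directly follows the explanation of who is enrolled, and Table 1 marks the GDS as a screening measure only, so it fits referral at screening. The point does not need the sentence: no section rules out starts or changes during the 24 weeks, and ordinary prescribing in response to mood would be enough.
3. **The wording may be loose.** Sex is given the same label, and Table 1 lists no medication record by visit, so baseline use may have been intended, and a fuller plan may say so. That is possible, but the sentence as published is a stated rule, and antidepressant use is the only item on which it has any effect. An analyst following it would enter current use.
4. **The simulation is not the planned analysis in every respect.** The plan log-transforms HAM-D-17, while the primary outcome is a proportion: "The primary outcome of the study is the proportion of participants who are classified as responders". The percentages come from an untransformed continuous outcome and do not carry over directly to either. They show that the shift can be nil, downward or upward, and nothing more precise.

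**Conclusion.** The concern holds as a matter of what is being estimated. The plan conditions on post-randomisation antidepressant use in its only named treatment-effect analysis, while claiming intention to treat in the same paragraph, and no other section restricts the covariate to baseline.

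The numerical consequence is unknown because the documents give no rate of starts or changes. Under the assumed scenarios it runs from negligible to about 20% attenuation or about 6% overstatement, and the larger figures need roughly a quarter to two fifths of controls to start a drug for reasons linked to mood. A reader might infer that the trial's result will necessarily be biased. The documents do not support that: if use does not depend on arm or mood, or if there is no true effect, no shift appears.

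The rule should be corrected, but as an inexpensive improvement and below the level of a must-fix.

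**What to change.** Replace the covariate sentence in Statistical analyses with:

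> Age, sex and antidepressant use at baseline will be included as fixed baseline covariates. Post-randomisation antidepressant changes will be tabulated by arm and will not be adjusted for in the primary model.

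This costs a sentence or two. Baseline use has to be known already, since the entry criterion depends on it. The tabulation needs medication to be recorded at follow-up visits, as the time-dependent covariate would also have done, so the sponsor should confirm that this happens. The article reports that recruitment was still under way, so at that stage the change could be made before outcome data by arm were examined.

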## Discussion

Since the prevalence of dementia doubles every 5 years after the age of 60, population ageing inevitably increases the number of persons with dementia. Hong Kong is no exception to this trend. It is estimated that around one in 10 local older persons are now suffering from dementia [50].

Caregiving for persons with dementia is demanding and challenging. Evidence shows that it adversely affects caregivers’ physical [51] as well as mental wellbeing [3–5], including a vulnerability to developing depression. In a review of 10 studies involving 790 caregivers of persons with dementia, more than one fifth of them suffered from a depressive disorder [3]. The prevalence of depressive symptoms among caregivers is even higher [14].

This study will investigate the efficacy of a structured exercise programme in alleviating depressive symptoms among caregivers of persons with dementia. We focus on caregivers with depressive symptoms instead of depressive disorders as the former constitute the largest group of depressed caregivers. Besides, because of ethical concerns, we will refer those who suffer from clinically significant depression to appropriate agencies for psychiatric assessment and treatment.

The intervention is tailor-made for family caregivers in three ways. First, the programme is delivered at participants’ homes to facilitate their participation. Second, both caregivers and care recipients will be involved in the study. Third, a moderate-intensity aerobic exercise that has been successfully implemented in the local older population (i.e. sitting Tai Chi) is chosen as the intervention.

Sitting Tai Chi is a safe, low-impact and low-cost exercise intervention. If it is shown to improve caregivers’ mood, it will offer a potentially effective treatment alternative for depression among caregivers of persons with dementia. In addition, we expect that home-based exercise will also benefit the care recipients.

## Trial status

The study is still recruiting at the time of submission.

## Abbreviations

ADL: Activities of daily living
BBS: Berg Balance Scale
BDNF: brain-derived neurotrophic factor
CONSORT: Consolidated Standards of Reporting Trials
CSDD: Cornell Scale for Depression in Dementia
CVFT: Category Verbal Fluency Test
DAD: Disability Assessment for Dementia
EXIT25: Executive Interview
FR: Functional Reach
GDS: Geriatric Depression Scale
HAM-D-17: Hamilton Rating Scale for Depression
IPIP: International Personality Item Pool
MBI: Modified Barthel Index
MCS: Mental component summary
MMSE: Mini Mental State Examination
NPI: Neuropsychiatric Inventory
PCS: Physical component summary
REC: Research Ethics Committee
SF-12: SF-12 Health Survey
SIGH-D: Structured interview guide for the Hamilton Depression Rating Scale
TUG: Timed Up and Go
ZBI: Zarit Burden Interview
